## Abstract

**Background:**

Pre-exposure prophylaxis (PrEP) is highly effective in preventing HIV transmission; yet, many people who would benefit from PrEP are not currently using it. Numerous programs and policies, including those provided under the US Ending the HIV Epidemic effort, have been implemented to increase PrEP use. Programs vary enormously, ranging from telemedicine PrEP support to electronic medical record prompts to social marketing and messaging campaigns. However, limited evidence exists regarding their relative impact on PrEP uptake.

**Objective:**

The aims of the PREMISE (PrEP Epidemiology, Modeling, and Surveillance) research program are to (1) provide context for PrEP scale-up in the United States, (2) assess the impact of different programs and policies on PrEP use, and (3) model the impact of PrEP-related programs and policies on population health.

**Methods:**

The primary outcomes of PrEP use and PrEP-to-need ratios will be extracted from a national medical data aggregator database that represents a majority of PrEP users in the United States. These data will inform all proposed analyses of the project: the dataset will allow the exploration of longitudinal trends in PrEP use by modality as a cohort study, it will be the outcome data for assessing changes associated with particular PrEP programs and policies for quasi-experiments, and it will provide baseline information to inform modeling regarding future impacts of PrEP policies and programs. The implementation of policies will be assessed using legal coding at the state level, and the implementation of programs across health jurisdictions will be assessed using a jurisdiction survey conducted in collaboration with participating health departments. Guided by a legal implementation framework, we will use descriptive and regression analyses to contextualize PrEP scale-up and use quasi-experimental designs to inform causal assessments of the effect of programs and policies. Here, we provide, as preliminary data, our extraction of PrEP prescribing from the national dataset.

**Results:**

This research was funded in August 2024. We obtained the national PrEP database and started data cleaning in March 2025. From 2016 to 2024, there were 20,394,619 claims for medications that were FDA-approved for PrEP, and we determined 13,644,979 claims to be PrEP prescriptions, representing over 1 million PrEP users. For medical benefit claims, there were 34,525 procedure claims for PrEP medications, and we determined 22,910 procedure claims to be for PrEP, representing over 6000 PrEP users.

**Conclusions:**

To optimally use HIV prevention resources, it is critical to understand the effects of different programs and policies. Over 1 million people have started PrEP, and tracking how this scale-up has occurred by PrEP modality and user groups will inform future HIV prevention efforts. By collaborating with health jurisdictions, we will provide systematic data regarding the panoply of programs and policies that have been enacted to support PrEP use.

**International Registered Report Identifier (IRRID):**

DERR1-10.2196/80911

## Introduction

### Background

The US Ending the HIV Epidemic (EHE) launched in 2019 and is led by the US Department of Health and Human Services. EHE sought to reduce new HIV infections and scale up HIV prevention and treatment strategies to improve health outcomes for populations and communities most affected by HIV [1]. A total of 57 jurisdictions across 26 states, as well as Washington, DC, and San Juan, Puerto Rico, have been prioritized in the US EHE initiative [2]. Among these 26 states, 48 counties across 19 states were prioritized due to significant HIV burden, and 7 additional states were prioritized due to substantial occurrence of HIV in rural areas [2].

Pre-exposure prophylaxis (PrEP) is highly effective in preventing HIV transmission and remains the centerpiece of HIV prevention efforts in the United States, yet the scale-up of PrEP has led to stark disparities by race and ethnicity, limiting its impact [3]. PrEP is well tolerated, available in inexpensive generic forms, and prevents over 99% of HIV transmission when taken as directed. In numerous areas, including the United States [4] and New South Wales [5], scale-up of PrEP has been associated with reductions in new HIV transmission at the population level. Despite the spectacular promise of PrEP, less than half of persons in the United States indicated for PrEP were taking it in 2024 [6]. From 2012 to 2017, PrEP use increased by an average of 56% annually [7], followed by a more gradual annual growth of 18% from 2018 to 2021 [3]. The PrEP-to-need ratio (PnR) is a measure of PrEP use that compares the number of PrEP users in a group or geographic area (numerator) to the number of HIV diagnoses (denominator) [8]. This metric has been used to measure PrEP uptake among groups that would most benefit from it in numerous studies and has been used in other areas such as the US Centers for Disease Control and Prevention’s (CDC) recent examination of mpox vaccine provision [9]. PnR assessments have revealed lower PrEP use among Black and Latinx persons, younger persons, women, and persons in the US South relative to epidemic burden [3,10]. Additionally, modeling suggests that the greatest overall HIV epidemic reduction occurs in scenarios with equal PrEP provision relative to HIV burden across racial groups (PnR=1) [11]. Thus, increasing uptake of PrEP in areas with greatest need, as defined by higher HIV incidence, maximizes the number of new infections averted for a given level of PrEP use. National disparities in PrEP provision by race, however, have increased over time [12]. There is an urgent need to identify policies and programs that improve PrEP uptake and PnR.

Despite substantial scale-up of PrEP attributable to past efforts and policies, legal and program environments in which PrEP-eligible people live are highly heterogeneous, and evidence regarding policy impact is lacking. The United States has made significant efforts to scale up HIV PrEP through EHE Programs, with over US $1.5 billion invested in HIV prevention from 2020 to 2024 [13]. EHE funding has been granted to the EHE priority jurisdictions through the Health Resources and Services Administration and CDC mechanisms that allowed state and local health departments and community health centers to implement HIV prevention and treatment initiatives. Diverse programs have been implemented with this funding—ranging from social media messaging to medical records improvements, and from clinician training to telemedicine PrEP prescribing [14-16]—yet, no research program has sought to determine the comparative effectiveness and efficiency of these PrEP interventions on a population basis to guide future investments. Outside of HIV EHE efforts, PrEP uptake may also be influenced by state-level policy decisions and the availability of CDC grant programs such as grants that were designed to support PrEP demonstration projects. Both Medicaid expansion and the use of Pre-Exposure Prophylaxis Drug Assistance Programs (PrEP DAP) offer promising approaches that are associated with increased PrEP use that is also more aligned with epidemic need [17]. It is critical to identify the program elements that have contributed most to successful outcomes within each PrEP service.

National prescription, medical, and diagnosis datasets using data from commercial entities are robust and capture a majority of all US prescriptions with line-level, deidentified individual data [17]. These comprehensive datasets enable accurate, nationwide data on PrEP prescribing, which can be used to develop valuable insights on HIV prevention efforts when analyzed in tandem with data regarding PrEP policies and programs provision. Moreover, such aggregated datasets allow for data to be rapidly assessed regarding the uptake of newer PrEP formulations and modalities (eg, long-acting injectable [LAI] PrEP medications), providing information regarding the use and care characteristics of newer PrEP modalities relative to previously approved modalities.

### Overview of Research Objectives

To support public health jurisdictions in reducing new HIV transmission, the consistent availability of national HIV PrEP data is essential. Such data can be used to describe patterns of PrEP use and to understand which programs and policies are effective at facilitating PrEP uptake, particularly among groups that will most benefit from PrEP use. The PREMISE (PrEP Epidemiology, Modeling, and Surveillance) research program aims to (1) provide context regarding the ways in which PrEP is being brought to scale in the United States, such as the use characteristics of different PrEP modalities; (2) describe the impact of health policies and programs on PrEP use and PnR in the United States; and (3) assess the characteristics of these policies and programs, their impact on population health, and their cost-effectiveness (Figure 1).

**Figure 1 figure1:**
[figure not shown]
PrEP Epidemiology, Modeling, and Surveillance (PREMISE) research program objectives overview. Overview of the 3 main PREMISE research program objectives, their corresponding study designs, and examples of the planned analyses. PnR: PrEP-to-need ratio; PrEP: pre-exposure prophylaxis; PrEP DAP: Pre-Exposure Prophylaxis Drug Assistance Program.

## Methods

### Research Setting and Population

The study population consists of patients who had claims between 2016 and 2024 for antiretroviral (ARV) medications approved by the Food and Drug Administration (FDA) for PrEP. Data on PrEP use are available from all 50 states, Washington, DC, and Puerto Rico. Objective 1 will use descriptive and exploratory assessments to contextualize PrEP scale-up. Objective 2 will compare trends in jurisdictions implementing a particular program versus a control group of jurisdictions not implementing that program. Selection of control jurisdictions will vary depending on the level of analysis: for instance, state-level analyses may include all states, whereas analyses at the county level may include counties that are matched by relevant characteristics such as HIV prevalence or county size. Data will be analyzed retrospectively from January 1, 2016, to December 31, 2024, and we will incorporate 4 future annual data updates for the years 2025 to 2028. This study period was selected because the PrEP dataset was considered by the data provider to be internally consistent in the way it was received from pharmacies over the time period, and allows for sufficient time before the launch of EHE programs in 2019. Objective 3 will model program effects for all EHE jurisdictions on future PrEP use based on an up to 20-year time horizon, expanding our team’s existing models for 6 EHE jurisdictions [18,19].

### Research Design Overview

Our analyses will use varied analytic approaches to answer our multiple research questions. To assess changes in PrEP provision over time (objective 1), we will use descriptive and modeling studies. To address gaps in understanding of what programs and policies will best facilitate PrEP scale-up and improved efficiency in the form of PnR (objective 2), we will use quasi-experimental approaches. Many policies and access programs influence PrEP access and uptake among states and over time. Therefore, we will use natural experiments to improve understanding of the impact on PrEP use by collecting information from jurisdictions regarding which programs were conducted and the dates of program operation. We will collect data regarding program characteristics and financial investment to improve our ability to assess causal relationships between different policies or programs and PrEP outcomes. Critical to this design is that, unlike randomized trials, it allows for assessment of health program outcomes with data from programs that were brought to scale outside of research settings by health jurisdictions. Such data will more accurately represent how health interventions are actualized in the United States. Objective 3 will use a mathematical modeling approach that is detailed below. For this paper, we followed the RECORD (Reporting of Studies Conducted Using Observational Routinely Collected Data) checklist (Multimedia Appendix 1) of items to be reported in observational studies using routinely collected health data [20].

### Conceptual Framework

Our inquiry will be grounded in a legal implementation framework that we have previously proposed to facilitate the development of health policies to optimally address infectious diseases (Figure 2) [21]. In this framework, now adapted to this research program, we posit law as a causal factor influencing HIV transmission. Here, we define law broadly, as sets of rules and regulations that are enforced by the government [22]. As seen in the model, law is enacted through institutions and can influence health positively through constructs such as insurance coverage of an otherwise unaffordable service, or negatively through adverse changes in coverage programs such as Medicaid. Other mechanisms are indirect; for example, wraparound services may assist clients in gaining stable housing, which may in turn facilitate medication adherence. Given this theoretical framework, changes in laws affecting PrEP provision have the potential to have substantial and long-lasting effects on vulnerability to HIV acquisition, including the provision of health services relative to needs for those services. Laws can be either a public health tool (eg, PrEP DAP programs) or a public health threat (eg, judicial rulings that may prevent the US Preventive Service Taskforce recommendations on PrEP from being binding for insurance coverage without cost sharing). Our research acknowledges the more proximal causes of persons taking or adhering to PrEP (eg, an individual’s perceived benefits of taking PrEP) and also focuses on programs and policies that shape and provide context for these decisions. We study programs and policies because (1) they are amenable to change, (2) they are measurable, and (3) there is plausibility that policies and programs can influence PrEP uptake. Relevant data sources will include legal coding and surveys to quantify programs and policies, census data to describe neighborhood factors, and PrEP claims databases to describe use and sociodemographic factors (eg, race, ethnicity, sex, and age). Due to the inherent limitations of our data sources, we cannot measure all components of the framework; instead, we will leverage it to inform the selection of data that are available.

**Figure 2 figure2:**
[figure not shown]
PrEP Epidemiology, Modeling, and Surveillance (PREMISE) research program legal implementation framework. Overview of the legal implementation framework used to guide the PREMISE research program and assess the impact of legal and policy changes on PrEP provision and uptake, and the corresponding data sources and planned analyses. PH: public health; PrEP: pre-exposure prophylaxis.

### Data Sources

This program of research will use three main data sources (see Table 1 for a summary of the variables of interest and covariates): (1) data from surveys of health jurisdictions and legal data extracted by the National Alliance of State and Territorial AIDS Directors (NASTAD), (2) a national PrEP database from a third-party data provider (prescription, procedure, and diagnosis claims datasets), and (3) US Census data. Other data sources as they become available will be included in analyses.

**Table 1 table1:** PrEP (pre-exposure prophylaxis) Epidemiology, Modeling, and Surveillance (PREMISE) research program variables and covariates: definitions and data sources^a^.

Construct			Levels or definition		Data source		Definition
**Primary explanatory variables**							
	Program type	Programs supporting PrEP^b^ initiation or retention		Health jurisdiction surveys and legal extraction data		Intervention program implemented	
	Funding spent	Dollars in staffing and direct costs expended to conduct each program		Health jurisdiction surveys		Surrogate for program magnitude	
**Primary outcomes**							
	PrEP starts	New PrEP users in each jurisdiction per time period		National PrEP database		PrEP initiation/population	
	PrEP start needs	New PrEP users, ratio-to-need in jurisdiction per time period		National PrEP database		PrEP initiation/HIV diagnoses	
	PrEP retention	User retained in care per time period		National PrEP database		Average retention time/population	
**Program covariates**							
	Funding	US Centers for Disease Control and Prevention, US Department of Health and Human Services, States		Health jurisdiction surveys and public records		Agency funding the program	
	Jurisdiction	County or state		Health jurisdiction surveys and legal extraction data		Jurisdiction operating the program	
**PrEP user and structural covariates**							
	Age (years)	18-24, 25-39, 40-54, 55 or older^c^		National PrEP database		Age of individual PrEP user	
	Race and ethnicity	Black, Latino or Hispanic, White, Asian, other^c^		National PrEP database		Race and ethnicity of individual PrEP user	
	Gender	Male and female^c^		National PrEP database		Self-identified gender of PrEP user	
	Copay	Average PrEP copay in dollars		National PrEP database		Copay of individual PrEP user	
	PrEP payer	Commercial, government, and other		National PrEP database		Insurer or payer of the PrEP prescription	
	Provider	National Provider Identifier		National PrEP database		Unique identification number of providers	
	Jurisdiction characteristics	% Bachelor’s degree holder, % living in poverty, % uninsured, % Black residents, % Latinx residents		US Census		Proportion of county residents with a characteristic	

^a^Summary of PREMISE research program constructs, including primary explanatory variables, primary outcomes, program covariates, and PrEP user and structural covariates, with corresponding levels or definitions. The table also lists data sources and how each variable is defined for analysis.

^b^PrEP: pre-exposure prophylaxis.

^c^Line-level data acquired from health exchanges. Granular data are not always available such as other identity and additional racial or age categories.

### Health Jurisdiction Survey

We will conduct a survey of health jurisdictions to understand which types of programs were provided in each jurisdiction over time and the degree of resources committed to implementing each program to obtain program data; these data will inform objective 2 analyses. Table 2 details the primary program types that we will assess, representing an array of program settings and types ranging from clinician training to electronic medical records changes to direct financial coverage of PrEP services. We will also assess community change mechanisms such as messaging campaigns and community-based organization-led PrEP outreach. Each of these mechanisms might feasibly impact PrEP use, so generating evidence on the relative impact of each program will be critical to guide future investments. The full text of the jurisdictional survey can be seen in Multimedia Appendix 2. Using lists of health jurisdiction members of NASTAD, we sent the survey to program staff representatives for each of the 50 states and the 8 jurisdictions that receive EHE funding independently from their state. Our instructions clarify that completing the survey may require the knowledge of multiple jurisdictional team members, and the survey is set up to facilitate this with a link that can be accessed by multiple respondents. Data collection launched in May 2025, accompanied by a webinar offered to all health jurisdictions to introduce the survey. We plan to complete data collection in the fall of 2025. To maximize the survey response rate, we will conduct outreach activities, including periodic email reminders, hosting open question and answer sessions, and individual support calls to engage jurisdictions to assist their survey completion.

**Table 2 table2:** PrEP (pre-exposure prophylaxis) Epidemiology, Modeling, and Surveillance (PREMISE) research program health jurisdictions, program types, and details^a^.

Setting and program type			Program details
**In-clinic programs**			
	Training for clinicians and clinical staff	Training or organizational capacity building to increase PrEP^b^ prescribing	
	EHR^c^ optimization	Changes to EHR to ease PrEP delivery: this includes electronic reminders for providers to assess a patient for PrEP eligibility or to develop a list of PrEP candidates using EHR data	
**External clinical programs**			
	Safety-Net PrEP Clinic	Delivery of PrEP through an existing STI^d^ clinic, community health center, pharmacy, or similar public health clinic, aimed at expanding PrEP access among key populations through reduced cost or free services	
	Telemedicine PrEP	Consists of full or hybrid telemedicine PrEP services that reduce or eliminate the need for in-person clinical visits	
	PrEP Assistance Program	Cover the cost of PrEP-related services, either directly or indirectly, usually by reimbursing providers for clinical visits and lab tests, or paying PrEP-related out-of-pocket costs to health plans	
	PrEP navigation services	Provide assistance to find a PrEP provider and address barriers to access PrEP, as well as support strategies to facilitate retention or reinitiation into PrEP care	
**Nonclinical programs**			
	Messaging campaigns	Digital or physical messaging, social marketing aimed at raising awareness about PrEP or sharing information about PrEP services available	
	PrEP outreach and education	Nonclinical outreach and education activities, typically delivered by staff or peers at community-based organizations focusing on raising awareness about PrEP, addressing misinformation, and sharing information about the availability of PrEP	

^a^Health jurisdictions program settings (in-clinic, external clinic, and nonclinical) with corresponding program types and program details. The program types will be assessed to understand which programs were implemented in each jurisdiction over time and the level of resources committed to each to obtain program data.

^b^PrEP: pre-exposure prophylaxis.

^c^EHR: electronic health record.

^d^STI: sexually transmitted infection.

We will also gather information on the passage and implementation of policies regarding PrEP at the state level through a systematic review of legislative records in existing state public health statutes and the legal database Westlaw. Data will be extracted, if available, regarding program types, program start or end dates, funding agencies, jurisdictions implementing the program, the program implementers, and the program financial expenditures. To improve data quality, we will optimize interrater reliability through clear definitions of domains, use raters who are familiar with the content area, and provide thorough training for raters through practice-based learning sessions. Validation of the dataset will be accomplished through conducting parallel extraction of independent coders to determine intercoder agreement for a proportion of the dataset.

### National PrEP Database (Prescription Claim, Procedure Claim, and Diagnosis Code Data)

We have obtained a national PrEP database through a contract with a third-party data provider—a health care company that aggregates national health data from clinics, providers, and pharmacies. This database includes prescription claim data, procedure claim data, and diagnosis claim data. PrEP medications can be billed through either pharmacy or medical benefits, depending on how the medication is dispensed (oral tablet or injection, pharmacy, hospital or clinic) and the requirements of the insurance plan. The diagnosis claim dataset contains medical conditions diagnosed using either the *ICD-9-CM* (*International Classification of Diseases, Ninth Edition, Clinical Modification*) or *ICD-10-CM* (*International Classification of Diseases, Tenth Edition, Clinical Modification*). For each deidentified person included in the database, the following variables are available: prescribed medication, date of each fill, number of pills or injections, sex, age, payer (Medicaid and private health insurance), and ZIP3 (the first 3 digits of a ZIP code). We will seek more specific user locations through both data crosswalks to the county level and providers’ practice location addresses. On June 18, 2025, lenacapavir was approved by the FDA as a twice-yearly LAI PrEP [23], and during the research period, we expect additional medications to be approved by the FDA for PrEP. Therefore, our data provider contract includes access to prescription data for lenacapavir and other potential future modalities.

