To understand the impact of PrEP policies and programs (objective 2), we will leverage the legal coding and health jurisdiction program provision datasets described above to conduct quasi-experiments with outcomes of PrEP starts, PnR, and retention in care. PrEP programs have been adopted by local health authorities in the context of the disbursement of EHE funds as grants to applicants. Despite the lack of random assignment of jurisdictions to policies and programs, we propose a quasi-experimental design that allows us to have findings that reflect several of the characteristics of randomized studies, including temporality and controlling for time-invariant factors. Although quasi-experimental approaches are subject to some limitations inherent to nonrandomized designs such as challenges in controlling for time-varying characteristics, these designs minimize bias relative to other analysis approaches. Moreover, quasi-experimental approaches improve upon the external validity of randomized studies because the data stem from programs that have been enacted in practice. Because of the study design, results will be well positioned to inform real-world programs such as those that comprise EHE efforts. For quasi-experiments, we will conduct analyses using methods such as difference-in-differences (DID) that account for intervention and control jurisdiction trends before program implementation. Because interventions are implemented at different points in time, we will use the heterogeneous DID method proposed by Callaway and Sant’Anna [32] or a similar method to account for potential confounding from multiple implementation periods. Health jurisdictions implementing a program or policy will be the primary intervention unit, and controls will be jurisdictions not implementing a program. DID analyses will be accomplished with regressions that include a term for group (eg, telemedicine PrEP program or not), period (month), and group-by-period interactions that serve to estimate the effect of the intervention. Our approach provides a relatively large sample size for such analyses, with many of the 50 counties or local jurisdictions funded under the EHE program implementing programs under assessment, and other non-EHE jurisdictions also implementing some of the identified programs. Control jurisdictions will be counties or states in the United States that do not implement a particular program, using 9 years of monthly PrEP use data (2016-2024). Depending on characteristics of the intervention, such as statewide provision, we may restrict the control group to jurisdictions meeting certain criteria in order to improve the match between intervention and control groups. For instance, we might match counties by HIV prevalence or jurisdiction size.

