
#### Power Calculation: Objective 2

The study design achieves 90% power to detect a minimum difference between intervention and control county PrEP rate means of 2.4 PrEP starts per 100,000 population. This is based on a sample size of 8,784,000 county-person-month observations, a figure obtained from a minimum estimate of 6 counties implementing a particular program and 238 control counties not implementing the program. We assume that each county has an average of 300 individual PrEP users (a conservative estimate because the 2021 average and median county PrEP users are 1210 and 482), and we assume an average of 60 months of follow-up (a conservative estimate because the total follow-up period is 144 months). The standard deviation of PrEP use at the county level is 73, and we conservatively assumed a small (0.05) within-person correlation. The power assessment is based on a time-by-treatment interaction test using a mixed-model analysis with a significance of 0.05. We performed a similar analysis for state-level policies and found a minimum detectable difference of <3 additional PrEP starts. Power calculations were performed in PASS 2022.

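### Users are located only to ZIP3, and no rule covers untreated counties that share a ZIP3 with an implementing county, so county-level effects will tend toward zero

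*Protocol article*

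**What the plan says.** In the Protocol article, National PrEP Database section, the only geographic variable listed for each person is "ZIP3 (the first 3 digits of a ZIP code". The article then states an intention: "We will seek more specific user locations through both data crosswalks to the county level", together with providers' "practice location addresses". Table 1 lists the National Provider Identifier ("Unique identification number of providers") as a database variable, so a link to practice addresses is feasible.

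Under Data Analyses (Objective 2), the control rule is: "Control jurisdictions will be counties or states in the United States that do not implement a particular program". The control group may be restricted to improve the match, and the example given is that "we might match counties by HIV prevalence or jurisdiction size". If parallel trends fail, the fallbacks include matching and synthetic control.

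The Power Calculation for Objective 2 takes counties as the comparison groups, with "a minimum estimate of 6 counties implementing a particular program and 238 control counties not implementing the program", and claims "90% power to detect a minimum difference between intervention and control county PrEP rate means of 2.4 PrEP starts per 100,000 population".

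No section says how to treat a non-implementing county that shares a ZIP3 with an implementing one. The Limitations section does not mention location error.

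**The concern.** Programs are assigned by county, but users are observed by ZIP3. If a ZIP3 covers one implementing county and one or more others, a crosswalk spreads the ZIP3's starts over all of them. Two things follow. The implementing county's outcome is diluted by its neighbours, and part of its effect is written into those neighbours. The neighbours meet the control rule, and matching on HIV prevalence or size does not remove them. Both effects push the estimate toward zero.

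The planned checks are not aimed at this. Event-study plots and pre-trend tests will tend to look better, not worse, when treated and control series are built partly from the same ZIP3 data. Placebo dates are run only for significant effects and guard against false positives, not attenuation.

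Effect and cost estimates feed the Objective 3 model. Program costs reported in the jurisdiction survey are not diluted, but the effects would be. Cost per additional start would therefore rise by 1/[w(1−q)], and an effective program could look weak or poor value.

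**Working it through.** **Inputs from the Power Calculation section:** 6 implementing and 238 control counties; 300 users per county; 60 months; SD 73; within-person correlation 0.05; significance level 0.05 (two-sided assumed); time-by-treatment interaction in a mixed model; 90% power.

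**Step 1: the plan's own figure.** The article does not give its formula. Of several forms tried, the slope-difference form using the stated 60 months fits:

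MDD = (1.960 + 1.282) × 73 × √[(0.95/Sxx) × (1/1800 + 1/71400)] × 59

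Here Sxx = 60(60² − 1)/12 = 17,995, 1800 = 6 × 300 and 71,400 = 238 × 300. The result is 2.42, against the stated 2.4. Nothing in this calculation allows for misallocated users. (Separately, 244 × 300 × 60 = 4,392,000, half the stated 8,784,000 observations. That is a different point and is not relied on here.)

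**Step 2: the attenuation factor.** Let the program raise the start rate by d in the treated county and by nothing elsewhere. Let w be the treated county's share of its ZIP3 population.

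- The ZIP3 rate rises by w·d.
- A crosswalk by population alone gives every county lying wholly in that ZIP3 the same rise, w·d.
- If a share q of controls lies in treated ZIP3s, the mean control rise is q·w·d.
- The expected estimate is w·d − q·w·d = w(1−q)·d.

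Within one such shared-ZIP3 pair the contrast is zero, whatever w is. If the county fills its ZIP3s and no control shares them, w = 1, q = 0 and nothing is lost.

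**Step 3: illustrative range.** The documents give neither w nor q, so all values below are assumed. Power = Φ(3.242 × factor − 1.960), which takes the plan's 90% at 2.4 as given.

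| w | q | w(1−q) | True 2.4 appears as | Power |
|---|---|---|---|---|
| 1 | 0 | 1.00 | 2.40 | 90% |
| 0.9 | 0 | 0.90 | 2.16 | 83.1% |
| 0.75 | 0 | 0.75 | 1.80 | 68.1% |
| 0.5 | 0 | 0.50 | 1.20 | 36.7% |
| 0.25 | 0 | 0.25 | 0.60 | 12.5% |
| 0.5 | 18/238 | 0.462 | 1.11 | 32.2% |
| 0.5 | 6/24 | 0.375 | 0.90 | 22.8% |

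The last row assumes a pool restricted to 24 controls. It keeps the standard error of the full pool, so its power is somewhat optimistic.

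**Step 4: which part matters.** With 238 controls, one shared control per treated county gives 1 − 6/238 = 0.975, and three give 1 − 18/238 = 0.924. Shared controls thus remove a further 2.5% to 7.6%, and w does most of the damage. The second factor becomes important when the pool is small (6/24 removes 25%) or when weights concentrate on a few donors. Synthetic control can do that: a county sharing the treated county's ZIP3 will have a similar crosswalked history before the program and is a natural candidate for a high weight.

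**The case against.** The strongest reply is that ZIP3 is not the plan's last word on location. The article also seeks provider practice addresses, and the provider identifier is in the data. Those addresses could give two counties in one ZIP3 different outcomes. This stands in part. The addresses are something to be sought rather than secured, and they place the prescriber, not the user. They help least for telemedicine PrEP, which is a surveyed program type and the article's own example of a treatment group. They reduce misallocation without removing it.

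A reader might infer that counties in one ZIP3 must receive identical outcomes, so that every county estimate is biased by construction. The documents do not support that. It requires counties lying wholly in one ZIP3, allocation by population alone and no use of provider data, whereas the article states no crosswalk weights. A county spanning several ZIP3s receives a blend. A reader might also take neighbouring controls as the main source of shrinkage; with 238 controls, step 4 shows otherwise.

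It is also fair that the matching criteria are only examples, so excluding shared-ZIP3 counties is compatible with the plan, and that an article may leave crosswalk detail to a fuller document. But the control rule it does state admits these counties, and nothing in it commits to removing them. State-level policy analyses are outside this point.

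**Conclusion.** The point holds for county-level Objective 2 analyses. User location is ZIP3, the control rule admits counties that may carry part of a treated county's signal, and neither the planned checks nor the limitations address the resulting pull toward zero. The direction rests on program effects being confined to implementing counties and on users being misallocated across the county boundary.

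The size is unknown. Under the limiting case of a pure population crosswalk, and with assumed w from 0.9 to 0.25 and no shared controls, a true 2.4 per 100,000 would appear as 2.16 down to 0.60. Provider addresses would lessen this by an amount the documents do not allow one to estimate. Dilution of the treated county's own rate is the main component; shared controls add little in the full pool and more in a restricted or weighted one. The stated detectable difference of 2.4 should be read as making no allowance for either.

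**What to change.** For county-level Objective 2 analyses:

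1. Exclude from the control pool, including any matched set or synthetic-control donor pool, every county sharing a ZIP3 with an implementing county. This needs a ZIP3-to-county lookup and costs some of the 238 controls. It removes the factor (1−q) but not w.
2. Add a sensitivity analysis that addresses w. Either restrict to implementing counties that make up most of their ZIP3s' population, or analyse at ZIP3 level with exposure coded as the population share living in implementing counties. The first loses treated counties from a minimum of 6. The second assumes effects linear in that share and replaces a binary treatment with a continuous one, which changes the planned staggered estimator. It therefore belongs as a sensitivity analysis, not the primary one.
3. Name the location error and its bias toward the null in the Limitations, and state that the 2.4 per 100,000 detectable difference does not allow for it.
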